## Abstract

**Background:**

The number of falls experienced by people with knee osteoarthritis (OA) is almost double the number experienced by people with no OA. The neuromuscular elements required to arrest a fall are more impaired in people with knee OA compared to their asymptomatic counterparts. Therefore, these elements may need to be incorporated into an exercise intervention to reduce the risk of falling. The aim of this study will be to examine the feasibility, safety and patient satisfaction of a high-speed resistance-training program, with and without balance exercises, in people with knee OA compared to a control group. The effect of these exercise programs on lower-limb muscle strength and physiological and functional risk factors for falls will also be examined.

**Methods:**

This study will be a pilot randomized controlled trial with a pre- and post-intervention design (outcome assessments at baseline and 8 weeks after participation commencement) comparing three groups: a control group (no intervention), a high-speed resistance-training group and a high-speed resistance-training plus balance exercises group. Thirty people with knee osteoarthritis aged 60–90 years will be recruited and randomized to one of the three groups. Feasibility and safety will be assessed by examining adherence to the exercise program, dropout rate, pain level during and following exercise, number of exercises stopped due to pain, and any adverse event or any incident that prevents the participant from completing the prescribed exercise. Secondary measures of lower-limb strength, physical function, self-reported pain and function, fear of falls, and executive function and quality of life will also be assessed. To determine statistical trends of effectiveness and hence to inform sample size for a fully powered study, analyses of the secondary outcomes will be performed to assess the changes within and between groups over time (pre-post) using repeated measure ANOVA.

**Discussion:**

The results of this study will improve understanding of what type of exercise is safe and beneficial for people with knee OA to reduce their risk of falling, and hence will inform the development of a future large research trial.

**Trial registration:**

Australian New Zealand Clinical Trials Registry, ID: ACTRN12616001382460. Registered on 6 October 2016.

**Electronic supplementary material:**

The online version of this article (doi:10.1186/s13063-017-2129-7) contains supplementary material, which is available to authorized users.

## Background

Falls in older people are a major public health problem with substantial economic health cost and significant implications for the individuals. Knee osteoarthritis (OA), a common painful, debilitating and life-altering joint disease, is present in 50% of adults over 65 years of age. The prevalence of falls in people with OA is substantially higher than in older individuals generally (30%), with approximately 50–60% of those with knee OA over the age of 60 years reporting one or more falls each year [1–3]. However, despite the high prevalence of falls in people with knee OA, the mechanism of falling in this group is unclear. Moreover, there are no randomized controlled trials demonstrating the effectiveness of different types of exercise or other fall-prevention approaches in reducing falls in people with OA.

Aging is associated with neuromuscular changes that affect the ability to maintain dynamic postural control during imbalance episodes such as slower muscle response, poorer muscle strength and muscle power. In people with knee OA, these neuromuscular deficits might be more impaired, leading to a greater risk of falling when rapid balance recovery responses are required such as when falling. In our previous research, we found that when simulating a forward fall, those with knee OA demonstrated slower step responses and an impaired ability of the knee joint to absorb impact forces and slow down the body’s forward momentum to arrest a fall [4]. These biomechanical responses observed in people with knee OA might be related to loss of muscle power, especially the quadriceps, which is the most commonly affected muscle in this patient group [5]. Muscle power reflects the ability of the muscle to produce force rapidly. Given that recovering balance requires a rapid response, exercises that target fast muscle activation might be effective in maintaining adequate muscle function to prevent falls in older people and in those with knee OA.

Exercise interventions that focus on balance exercises have been shown to be effective in reducing falls for older people [6]. However, there is no evidence to suggest that current fall-prevention programs will be effective for people with knee OA. Moreover, existing exercise-based fall-prevention programs mainly focus on maintenance of balance and do not focus on training the neuromuscular elements required to arrest a fall. The neuromuscular elements required to arrest a fall are more impaired in people with knee OA compared to their asymptomatic counterparts [4]. To recover balance from falling, adequate muscle force and joint power generation is required [7]. This is adversely affected by OA. Hence, these unique factors and the associated pain must be taken into account in the design of fall-prevention strategies in this high-risk group. Consequently, development of an exercise approach aimed at reducing falls that is specifically designed to address these neuromuscular factors for people with knee OA is essential.

In this study we aim to examine the feasibility, safety and patient satisfaction of a high-speed resistance-training program, with and without balance exercises, in people with knee OA compared to a control group. Given the pain associated with knee OA, it is crucial to determine what effect high-speed resistance training that focuses on muscle power has on knee pain. This is of particular importance as this mode of exercise may potentially increase impact load on the knee joint due to the rapid and powerful movements involved. Therefore, feasibility and safety of the proposed exercise intervention must be assessed to determine if this exercise approach is safe to prescribe for those with knee OA. The effect of the exercise interventions on strength, physiological and functional risk factors for falls, pain, and executive function will also be assessed to provide data to support a sample size calculation for a fully powered trial.

## Methods

All procedures involved in this trial will be conducted in compliance with the National Statement on Ethical Human Resource and the Australian Code for the Responsible Conduct of Research. Ethical approval has been obtained from the Human Research Ethics Committee from Victoria University, Melbourne (Application ID: HRE15-285). All participants will provide written informed consent. The study was designed according to the Consolidated Standard of Reporting Trials (CONSORT) guidelines and the Standard Protocol Items: Recommendations for Interventional Trials (SPIRIT) 2013 Checklist (see Additional file 1) and publications associated with the trial will be reported according the CONSORT 2010 Statement [8]. The trial has been retrospectively registered in the Australian New Zealand Clinical Trials Registry (ACTRN12616001382460).

### Design and setting

This study is a pilot randomized controlled trial with a pre- and post-intervention design (outcome assessments at baseline and at 8 weeks after participation commencement) comparing three groups: a control group (no intervention), a high-speed resistance-training program and a high-speed resistance-training plus balance exercises program. The groups will be assessed before and after the 8-week program to examine the effect of the intervention on pain, adherence to the intervention, lower-limb muscle strength, physiological and functional risk factors for falls, executive function, fear of falling, quality of life and participant perceptions of the interventions.

#### Participants

Participants aged 60–90 years with knee OA who have had a fall in the previous 12 months, or who are concerned about having a fall, will be recruited. Clinical diagnosis of knee OA based on the American College of Rheumatology will be used [9].

Inclusion criteria: participants will need to have had knee pain for at least 6 months and experience current average pain of at least 3 (on an 11-point Numerical Pain Rating Scale (NRS)) and be able to ambulate independently (with no more than a single-point stick used for ambulation). A total of 30 participants will be recruited (10 per group).

In addition to the above criteria, participants will also have to have one of the following criteria indicating increased risk of falling: (1) have had at least one fall in the past 12 months and (2) have limited their activity level due to concern about falling. Including people who are concerned about falling (with or without falls) will increase recruitment, and maintain a group at increased risk of falls, as activity limitation is often associated with reduced balance and mobility [10].

Participants will be excluded from this study if they have: (1) any uncontrolled nonmusculoskeletal conditions that would make testing difficult and uncomfortable such as chronic obstructive airways disease and/or congestive heart failure, (2) a pre-existing neurological condition that affects lower-limb strength, balance and or ambulation (e.g., polio, stroke), (3) any uncontrolled musculoskeletal or orthopedic conditions that may affect ambulation (e.g rheumatoid arthritis), (4) current involvement in a structured resistance-training and/or an organized balance-training program more than once a week, (5) any documented medical condition or physical impairment that is deemed by the medical practitioner to contraindicate their inclusion and (6) mild cognitive impairment or dementia determined by a score of less than 25 using the Saint Louis University Mental Status (SLUMS) test [11].

### Procedure

The procedure is outlined in Fig. 1. Preliminary screening will be conducted over the telephone by one of the researchers. Volunteers who are deemed eligible will be scheduled a first visit. All participants will undergo the following physiological and functional assessments including lower-limb strength and proprioception, functional and balance tasks and executive function tests. Moreover, measures of physical activity, quality of life, pain and function, fear of falls, as well as falls history, will also be recorded. Participants’ satisfaction with the exercise program and their perception of improvement will also be assessed at the follow-up visit at the completion of the 8-week intervention. Figure 2 outlines the study design schedule in accordance with the SPIRIT Figure.

**Fig. 1 Fig1:**
[figure not shown]
Flow diagram of study procedure, recruitments and randomisation

**Fig. 2 Fig2:**
[figure not shown]
Study design schedule in accordance with the Standard Protocol Items: Recommendations for Interventional Trials (SPIRIT) Figure

Participants will first attend the Victoria University Footscray Park campus for baseline testing. During the first visit all measures, excluding strength, will be assessed. Familiarisation with the strength test will be conducted in the first visit followed by actual testing during a second visit (approximately 3–6 days apart). A set of questions to assess cognitive impairment (memory) will also be conducted in the initial visit using the SLUMS test where participants who score below 25 cut-off scores will be excluded from the study [11]. In the second visit, after completion of the strength test, participants will be randomized to one of the three groups: (1) high-speed resistance-training (HSRT) or (2) high-speed resistance-training and balance exercises (HSRTB) or (3) control group (no intervention). All eligible participants will complete the Exercise and Sport Science Australia (ESSA) exercise screening tool to evaluate any contraindicated medical conditions to exercise (https://www.essa.org.au/wp-content/uploads/2011/09/Screen-tool-version-v1.1.pdf). Participants answering “yes” to any of the screening questions will be required to obtain medical clearance from their local physician prior to participation in the intervention. Only participants randomized to one of the exercise intervention groups will need to obtain medical clearance if deemed relevant. Participants in the exercise intervention groups will attend Victoria University Exercise Rehabilitation Clinic twice a week for 8 weeks (total of 16 exercise sessions). Participants from the control group will be advised to continue with their usual activities. All participants will be reassessed after 8 weeks from the baseline assessment.

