## Secondary outcomes

Demographic information including falls history (and associated information surrounding circumstances of falls), duration of joint symptoms, comorbidities, medical conditions and medications will be collected.

The following functional, physiological and cognitive tests will be assessed at baseline and at the follow-up assessment. These selected tests are key measures used to identify risk of falls:Leg strength and endurance will be assessed using the 30 s chair stand test. Participants will sit on a chair (a 43-cm high chair) and stand up, then repeat, as many times as they can for 30 s (no upper limb support), the number of sit to stand efforts performed will be recorded [21]Physical function will be assessed using the Timed Get Up and Go Test (with and without dual tasks (manual and cognitive)) [22]. Participants will stand up from a chair, walk 3 m as quickly and safely as possible, cross a line marked on the floor, turn around and walk back and sit down. This test will also be performed when carrying a glass of water (manual dual task) and when counting backward by 3’s (cognitive dual task). The time taken to complete the task will be measured with a stopwatch. One practice trial will be given followed by an actual testA rapid dynamic weight shift, coordination and stepping will be assessed using The Four Square Step Test (FSST) of balance [23]. Participants will step as fast as possible into four squares marked on the floor with tape (labeled 1–4) in a certain sequence (starting from square 1 then 2, 3, 4, 1, 4, 3, 2 and 1). This sequence requires the participant to step forward, backward, and sideways to the right and left. The score will be recorded as the time taken to complete the sequenceFunctional muscle power will be assessed using the Timed Stair Climb Test (10 steps, 14-cm rise). The time taken to complete the task (climb 10 steps as quickly as possible) will be recorded and the stair climbing power will be calculated using a formula described in previous research [24]Static balance will be assessed by evaluating postural sway of the body in the medio-lateral (M/L) and anterior posterior (A/P) directions using a swaymeter while standing on a medium-density foam rubber mat (70 × 60 × 15 cm thickness) with the eyes open and closed. The total excursion of the sway in each direction is measured in millimeters [25]Knee proprioception will be measured during sitting by matching the position of the legs on either side of a clear plastic sheet with the eyes closed [3]. Any error in matching the limbs will be recorded in degrees. After two practice trials, the average of five trials will be recordedThe ability of older people to step maximally and rapidly in multiple directions will be assessed using the Maximum Step Length and Rapid Step Test [26]. Initially, the maximum step length in the front, side and back directions will be assessed. With arms crossed over the chest, the participant will step maximally with one leg while keeping the other leg planted and then to return to the initial position in one step. The test will be repeated for each leg in three directions (front, side, back). Three practice trials will be given followed by a series of five trials for each leg in each direction. The step length will be measured and the average of the five trials will be used for the rapid step test. For the rapid step test, marks on the floor will be placed at 80% of the maximum step length measured previously in each direction. Participants will then step as fast as possible with one leg in a given direction on the marks on the floor as instructed by the assessor. A practice set of four steps for each leg will be given. The actual testing will include a series of 24 steps randomly selected by the assessor which will include four steps in each direction for each leg. The total time taken to complete the step sequence and any errors will be measured. An error will be defined as (1) loss of balance, (2) failure to return to the initial position, (3) multiple steps and (4) noncompliance with direction or sideLower-limb muscle strength will be assessed by having participants perform three maximal repetitions (3RM) during bilateral leg press using a seated leg-press machine. The maximum amount of weight lifted by participants through three full-range repetitions while maintaining correct technique will be used for determining the participant’s maximum 3RM strength. Participants will have a familiarisation session before the actual recording of the 3RM test. During the familiarisation session participants will be shown the correct exercise technique and be given the opportunity to familiarise themselves with the exercise. Initially, each participant will perform a warm-up set of eight repetitions on the leg press with a light load. This will then be followed by the completion of five to six repetitions at a heavier weight and rest period of 2–3 min. The load will be increased incrementally until only three repetitions with correct technique are able to be completed

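### Physician clearance after a positive ESSA exercise screen comes too late and only in the exercise arms, so it never covers the baseline 3RM and fastest-effort tests, nor the controls' week-8 retest

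*Protocol article*

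**What the plan says.** The order of events is set out in the protocol article, Methods, Procedure and the text following Fig. 2.

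- **Telephone screening** by a researcher comes first: "Volunteers who are deemed eligible will be scheduled a first visit".
- **Visit 1:** "During the first visit all measures, excluding strength, will be assessed". Familiarisation with the strength test also takes place here.
- **Visit 2**, about 3–6 days later, is the 3RM leg press and then allocation: "In the second visit, after completion of the strength test, participants will be randomized to one of the three groups".
- **ESSA tool:** "All eligible participants will complete the Exercise and Sport Science Australia (ESSA) exercise screening tool to evaluate any contraindicated medical conditions to exercise". The text names no visit for it.
- **After a positive answer**, participants "will be required to obtain medical clearance from their local physician prior to participation in the intervention".
- **Restriction:** "Only participants randomized to one of the exercise intervention groups will need to obtain medical clearance if deemed relevant".

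Under Secondary outcomes, the "functional, physiological and cognitive tests will be assessed at baseline and at the follow-up assessment". These include a timed stair climb, the Four Square Step Test and a rapid step test, all done at the participant's fastest, and the 3RM leg press, for which "The load will be increased incrementally until only three repetitions with correct technique are able to be completed". The Procedure text has all participants, controls included, reassessed at 8 weeks.

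**The concern.** The protocol has its own trigger for a physician's review of fitness to exercise, but does not apply it to the most demanding single efforts in the assessments. People aged 60–90 whose answers call for review lift the heaviest load they can manage three times, and climb and step as fast as they can, before that review is due. Controls do so twice and never need it.

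There is also a cost to the trial itself. Because clearance is sought after allocation and only in two of the three arms, someone found medically unsuitable becomes a post-randomisation loss in an exercise arm, while an equally unsuitable control stays in and is retested. Completion and dropout are primary measures (Feasibility and safety outcomes), so what is really a screening failure could be counted as poor feasibility of the exercise. The one-sided loss would also enter the between-group pre–post analysis that is meant to inform the next trial's sample size (Statistical analysis approach).

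**Working it through.** **Sequence.** This part needs no arithmetic; the statements only have to be put in order.

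1. Visit 1: all non-strength measures, including the fastest-effort tests, plus strength familiarisation.
2. Visit 2: 3RM leg press.
3. Visit 2, after the 3RM: randomisation.
4. Before the intervention: clearance, for ESSA-positive participants in the two exercise arms only.
5. Week 8: all three arms retested.

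The duty to obtain clearance depends on allocation (step 3), and allocation follows every baseline test (steps 1 and 2). The duty therefore cannot arise before baseline testing, at whichever visit the form is filled in. For controls it never arises.

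**Scale.** The plan gives no figure to reproduce. The planned size is 30, with 10 per group (Participants). Two inputs are assumptions:

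- *p*, share ESSA-positive: 0.10 to 0.60
- *r*, share of ESSA-positive participants whose physician refuses clearance: 0.05 to 0.20

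| Quantity | Formula | Low | High |
|---|---|---|---|
| Tested at baseline with no review required | 30 × p | 3 | 18 |
| Controls retested at week 8 with none required | 10 × p | 1 | 6 |
| Total such assessments | 40 × p | 4 | 24 |
| Exercise-arm participants needing clearance | 20 × p | 2 | 12 |
| Lost to refusal after randomisation | 20 × p × r | 2 × 0.05 = 0.1 | 12 × 0.20 = 2.4 |
| Controls who would have been refused but stay in | 10 × p × r | 1 × 0.05 = 0.05 | 6 × 0.20 = 1.2 |

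One person is 1/10 = 10% of a single arm, or 1/20 = 5% of the two exercise arms combined, so a single refusal visibly moves a completion or dropout percentage.

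**The case against.** The best defence is that the protocol works in two tiers: eligibility criteria govern assessment, and physician clearance governs training. Exclusion 1 is worded around conditions that would make testing difficult. Exclusions 2 and 3 remove neurological and uncontrolled musculoskeletal conditions. Exclusion 5 removes documented conditions that a medical practitioner judges to contraindicate inclusion. Telephone screening precedes visit 1. The exposures also differ: training is 16 sessions rising to 60–80% of one-repetition maximum, whereas most assessments are brief and the 3RM has a familiarisation session, a warm-up set and graded loading. A positive answer is not itself a contraindication. The ranges above are guesses, and Figs 1 and 2 are not available to check.

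Much of this stands as mitigation. It reduces the number at risk and the hazard per test, and the 3RM is the clearest case; the brief walking and stepping tests matter less. Exclusion 5 can also remove some people before randomisation, so the refusals left are those newly prompted by the ESSA tool.

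It does not close the gap. Exclusion 5 needs a documented condition and a practitioner's judgement, and nothing in the text makes a positive ESSA answer prompt that judgement before testing, or at any time in controls. Familiarisation and graded loading are not medical review. Nor is this detail left to a fuller document: the article says who needs clearance and when.

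It is also fair that refusals are informative in a feasibility pilot. They would be more informative as screening failures counted in all volunteers than as dropouts in two arms.

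**Conclusion.** The concern holds. As written, no ESSA-positive participant needs physician review before the baseline 3RM and fastest-effort tests, and ESSA-positive controls need none before the retest. This follows from the stated order and depends on no assumed rate. The number affected cannot be known from the article. The ranges of 3–18 people at baseline, 1–6 controls at week 8 and 0.1–2.4 post-randomisation losses rest entirely on the assumed 10–60% positive and 5–20% refused, and the lower end of the last range is effectively nobody. Given the existing exclusions and the precautions around the 3RM, this is a change that should be made rather than a fault that invalidates the trial.

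**What to change.** - Have every volunteer complete the ESSA tool at telephone screening, or at the latest at the start of visit 1 before any performance test or strength familiarisation. Telephone screening is preferable, because a letter can then be obtained before visit 1 and no visit has to be rebooked.
- For any positive answer, require physician clearance before the baseline performance and 3RM tests, and so before randomisation, in all three arms.
- Delete the sentence limiting clearance to the exercise groups.
- Count refusals as screening failures and report their number.

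The questionnaire is already planned for everyone, so the new burden is a letter for ESSA-positive future controls (about 1–6 of 10 under the assumed range) and an earlier letter, with a short wait, for the others. Some volunteers may not return, which matters with 30 places, but losing them before randomisation does less harm than losing them after it.

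Recruitment is ongoing (Trial status), so this is a mid-trial change to enrolment that would need ethics approval, and early and late participants will have been screened differently. The date of the change should be reported. ESSA-positive controls already enrolled can be asked for clearance before their week-8 tests.

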## Exercise protocol and familiarisation sessions

Participants will undergo up to two familiarisation sessions prior to commencement of the intervention to ensure that they feel comfortable with the exercises and perform them with the correct technique. To determine the training load (resistance weight to be lifted) for the high-speed resistance-training exercises for each participant, an estimation of their one repetition maximum (or 1RM) will be calculated indirectly using submaximal estimation [15]. Participants will perform between 7 and 10 repetitions of each exercise with the maximum weight that they could lift. Participants performing the weight-bearing exercises (such as sit to stand, squat, calf raises) will initially use their body weight only. Additional weight (using a vest weight) will then be added as needed. Their estimated 1RM will be then used to determine the relative load/resistance required for the training protocol as detailed below.

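### The follow-up visit has conflicting anchors, so exercisers are either tested with almost no room to finish the 8-week program or tested at a longer interval than controls

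*Protocol article*

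**What the plan says.** The protocol article times the single follow-up assessment in three ways.

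- **From baseline.** Procedure (text after Fig. 2): "All participants will be reassessed after 8 weeks from the baseline assessment".
- **From the start of participation.** Design and setting: "outcome assessments at baseline and at 8 weeks after participation commencement". The Abstract repeats this. The starting event is not defined.
- **From the end of the program.** Procedure (opening paragraph) has satisfaction and perceived improvement recorded "at the follow-up visit at the completion of the 8-week intervention". Design and setting adds: "The groups will be assessed before and after the 8-week program".

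The steps before training are also described. At baseline, "During the first visit all measures, excluding strength, will be assessed"; strength is tested at a second visit about 3 to 6 days later. Allocation comes at the end of that visit: "In the second visit, after completion of the strength test, participants will be randomized to one of the three groups". Participants with a positive answer on the exercise screening tool need a physician's clearance before training, and this applies to the exercise arms only. Under Exercise protocol and familiarisation sessions: "Participants will undergo up to two familiarisation sessions prior to commencement of the intervention". The program is then two sessions a week for 8 weeks, 16 in all.

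The Statistical analysis approach compares the three arms by repeated-measures ANOVA with a two-level time factor, before and after the intervention. The results are meant to supply power calculations for a full trial.

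**The concern.** The three anchors coincide only if training starts on the day of the baseline assessment, and the protocol's own sequence puts several steps between the two. Those steps fall mainly on the exercise arms: clearance explicitly so, and familiarisation with the training exercises by its nature. The delay is therefore not shared equally by the three arms.

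Either way of resolving the conflict has a cost. If the visit is held 8 weeks from baseline, most exercisers are measured before the program ends, and the sessions still to come belong to Phase 3. Satisfaction with the program and pain at its completion would then be recorded early. If the visit waits for the program to end, exercisers are measured later than controls, who have nothing to complete. The time factor then stands for different intervals in different arms, and the group-by-time contrast mixes treatment with elapsed time. Whatever distortion results is carried into the planning of the full trial.

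**Working it through.** **Program length.** 2 sessions per week × 8 weeks = 16, and by phase 4 + 6 + 6 = 16. The protocol's figure is reproduced.

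**Inputs from the protocol.** Visit 1 = day 0. Visit 2 and randomisation = day 3 to day 6. Program = 16 sessions at two a week.

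**Input assumed.** The lag from visit 2 to the first training session is not given. I used 0, 7, 14 and 21 days.

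**Span of 16 sessions.** With gaps alternating 3 and 4 days there are 15 gaps: 8 × 3 + 7 × 4 = 52 days from first session to last. The program's full 8 weeks are 56 days.

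**When all 16 sessions fit.**
- Counting 8 weeks from visit 1: the first session must fall by day 56 − 52 = 4. Visit 2 would have to be on day 3 or 4, with training starting that day or at most one day later.
- Counting from visit 2: the lag can be at most 56 − 52 = 4 days.

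Neither leaves much room for clearance or familiarisation.

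**Sessions done and interval, by assumed lag.** First session on day s = (3 to 6) + lag. Sessions done by the test day are those with session day ≤ 56 (from visit 1), or ≤ visit 2 day + 56 (from visit 2). Interval from visit 1 to program end = (s + 56) / 7 weeks.

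| Lag after visit 2 (days, assumed) | Sessions done, 8 weeks from visit 1 | Sessions done, 8 weeks from visit 2 | Weeks from visit 1 to program end |
|---|---|---|---|
| 0 | 15–16 | 16 | 8.4–8.9 |
| 7 | 13–14 | 15 | 9.4–9.9 |
| 14 | 11–12 | 13 | 10.4–10.9 |
| 21 | 9–10 | 11 | 11.4–11.9 |

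Example, lag 7 days. With visit 2 on day 3, s = 10 and 56 − 10 = 46 days remain; the 14th session falls 45 days after the first and the 15th at 49, so 14 are done. With visit 2 on day 6, s = 13 and 43 days remain; the 13th falls at 42 days and the 14th at 45, so 13 are done. Program end is (10 + 56) / 7 = 9.4 or (13 + 56) / 7 = 9.9 weeks.

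**Difference between arms if exercisers are tested at program end.** Controls at 8 weeks from visit 1; exercisers between 59 / 7 = 8.4 weeks (visit 2 on day 3, no lag) and 83 / 7 = 11.9 weeks (visit 2 on day 6, 21-day lag). The difference is about 0.4 to 3.9 weeks.

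**The case against.** The best defence is that the intent is clear. Design and setting has the groups assessed before and after the program, the opening of Procedure puts follow-up at completion, and the start of participation may simply mean the start of training. On that view the sentence tied to the baseline assessment is loosely worded, and nobody plans to test people mid-program. Baseline could also fairly be dated from visit 2, since strength is measured only then. Familiarisation may be short or absent, and clearance concerns only some exercisers. Figs. 1 and 2 are not shown and may fix the visit.

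Much of this stands. It makes early testing the less likely plan and may reduce three anchors to two. But it does not date the controls' visit: if exercisers are tested at completion, the only explicit date for controls is still 8 weeks from baseline, and the arms differ. A clear figure would leave the text in conflict with itself.

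Two stronger readings are tempting and should not be drawn. A reader might infer that no exerciser can finish by 8 weeks from baseline. That is too strong: 16 twice-weekly sessions span about 52 days and can just fit after an immediate start. A reader might also infer that the primary completion and attendance figures are distorted. The protocol nowhere says that training stops, or that completion is judged, at the reassessment visit, so this is not shown.

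**Conclusion.** The contradiction in visit timing is in the text and does not depend on any assumption. Read literally from visit 1, the schedule leaves little or no room to finish the program. Read as testing at completion, it sees exercisers at about 8.4–11.9 weeks against 8 weeks for controls. The size of either effect rests on assumed lags of 0 to 21 days after visit 2 and on evenly spaced twice-weekly sessions.

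The consequence is confined to what is measured at follow-up, chiefly the secondary pre-post comparisons of a 30-person pilot. The documents give no basis for putting a figure on the resulting bias. It still deserves correction, because the timing difference depends on arm, the comparisons feed the next trial's power calculation, and an analysis cannot restore equal intervals once the visits have taken place.

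**What to change.** Reconcile the Abstract, Design and setting, and both statements in Procedure to one anchor that applies to all three arms. One workable form is a common target date counted from randomisation, equal to the planned lead-in plus 8 weeks, with a stated window. It would apply regardless of the number of sessions completed, and controls would have the same target date. Either define the start of participation or drop the term.

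The cost is a wording change and a scheduling rule, with no extra visits. Control visits move later by the length of the lead-in. Exercisers with a short lead-in will have a brief gap between their last session and testing, and those whose lead-in exceeds the planned one may still be training when tested; the window should be chosen with both in mind. Recruitment is described as ongoing, so the change can still help. For anyone already followed up, report the actual interval from randomisation to follow-up by arm.
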